At the end of 2 weeks, the app will automatically discontinue EMA surveys. Two 1-week EMA phases will occur during the randomized period (weeks 1 and 8 post randomization; Figure 1). Staff will re-train participants on the EMA app prior to each of these EMA phases. Staff members will monitor EMA compliance and will reach out proactively to participants failing to meet criteria. After the third and final EMA phase, participants will be reminded that they will no longer need the EMA app, and that they can delete it (see figure 1 study schema for illustration of EMA administration periods).

All EMA surveys, regardless of phase of the study, will consist of short, multiple-choice items with logic-branched follow-up items. Within each of these surveys, participants will be queried on social settings and activities, cannabis and other substance use, mood, and suicidal ideation. See sections below detailing our plan for data monitoring to ensure safety in the event of SI exacerbation.

**Actigraphy Component (Fitbit): P**articipants will participate in a study component that collects sleep and activity data via a Fitbit Inspire 3. Participants will wear the watch after enrollment at Visit 1 through the Visit 12 (approximately 70 days after enrollment). To enhance compliance, participants will be paid a $25 compliance bonus at each of the three EMA phases data is available for 16/24 hours of 80% of days within that phase.

| **Passive Parental Consent** | **Parental/student consent/assent** |  | **Cannabis users in CM discontinue cannabis use** |  |  |  |  |  |  |  |  |  |  |  |  |
| --- | --- | --- | --- | --- | --- | --- | --- | --- | --- | --- | --- | --- | --- | --- | --- |
|  | **V0** |  | **BL (V1)** | **V2** | **V3** | **V4** | **V5** | **V6** | **V7** | **V8** | **V9** | **V10** | **V11** | **V12** | **Exit interview** |
| Days since Baseline |  |  | 0 | 14 | 16 | 19 | 21 | 28 | 35 | 42 | 49 | 56 | 63 | 70 |  |
| Fitbit Inspire 3 |  |  | x | x | x | x | x | x | x | x | x | x | x | x |  |
| Phone Screener | x |  |  |  |  |  |  |  |  |  |  |  |  |  |  |
| EMA Assessments  (x indicates when EMA assessment phases begin) |  |  | x | x |  |  |  |  |  |  |  |  | x |  |  |
| *Substance Use Questionnaires* |  |  |  |  |  |  |  |  |  |  |  |  |  |  |  |
| AUDIT |  |  | x |  |  |  |  |  |  |  |  |  |  |  |  |
| CUDIT |  |  | x |  |  |  |  |  |  |  |  |  |  |  |  |
| CWS |  |  | x | x | x | x | x | x | x | x | x | x | x | x |  |

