**Fitbit Protocol:** The purpose of the Fitbit portion of the study is to assess whether cannabis abstinence impacts objective measures of sleep in school-aged adolescents and young adults. At Baseline, participants will receive a Fitbit 3 that is paired with a premade, de-identified account. At the first visit, participants will be instructed on how to use the device, including charging and syncing. Participants will then be instructed to wear the device at all times (except when charging the device), from Baseline (Visit 1) through Visit 12 (approximately 70 days after Baseline). Participants will be instructed to sync their device frequently throughout the study. At each visit, a member of study staff will also sync the Fitbit to the Fitbit app to pair the deidentified sleep and activity data to the pre-made de-identified account.

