Payments will be made using an escalating scale for abstinence reimbursements and on a consistent scale for EMA compliance (see Tables 1 & 2). The reimbursement schedule was informed by PI’s ongoing contingency management studies and has been effective in other populations (Worden et al., 2017). Maximum total earnings will be matched across group to not confound the potential effects of monetary payments and depressive symptoms and SI. Attendance payments paid via Advarra will be issued at the end of every in-person visit (when participants provide urine samples), abstinence payments will be made between visits when abstinence is biochemically confirmed, and EMA payments will be issued at the end of each of the three EMA phases.

| **Table 2: Max Overall Study Remuneration Schedule** | |
| --- | --- |
| **EMA Compliance Phase 1 (approximately 80%) completion** | $100 |
| **Or: EMA Compliance Phase 1 (approximately 50%) completion** | $25 |
| **Fitbit Compliance Phase 1 (66%) completion** | $25 |
| **EMA Compliance Phase 2 (approximately 80%) completion** | $100 |
| **Or: EMA Compliance Phase 2 (approximately 50%) completion** | $25 |
| **Fitbit Compliance Phase 2 (66%) completion** | $25 |
| **EMA Compliance Phase 3 (approximately 80%) completion** | $100 |
| **Or: EMA Compliance Phase 3 (approximately 50%) completion** | $25 |
| **Fitbit Compliance Phase 3 (66%) completion** | $25 |
| **Study Visits/ Abstinence** | $445 |
| **Overall Fitbit and EMA Bonus (completion across whole study)** | $50 |
| **Max Total Earnings $870** | |

Participants will earn either $100 for a compliance rate of approximately 80% or $25 for a compliance rate of approximately 50% across each of the three EMA phases and $25 for a Fitbit compliance rate of 66% across each of the three phases. Participants can earn an additional $50 if they achieve an overall compliance rate for both Fitbits and EMA phases across the entire study. Payments will be made at the study completion. If a Fitbit device is lost or not returned, 20% of the total earned for this portion of the study will be deducted.

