exploratory analyses for hypotheses 1.1 – 2.2 looking at all 5 individual items for suicidal ideation. To examine the impact of participants who are versus are not receiving mental health treatment, we will conduct a set of exploratory analyses for hypothesis 1.1 – 2.2 including a binary indicator for receipt of mental health treatment as an additional covariate. Additionally, we will conduct exploratory analyses for sleep and circadian rhythms. Sleep, circadian, and physical activity exploratory Fitbit metrics include: *Sleep duration*: mean and standard deviation [StD]) over the main sleep period, the day, and 24hrs; short (<6 hrs) and long (>9hrs) mean nocturnal sleep duration; *Sleep fragmentation*: Mean and StD of 7-day sleep efficiency and wake after sleep onset; *Sleep timing placement*: Mean sleep onset, offset, and mid-point; categorized also as advanced (sleep onset <0900) and delayed (sleep onset >0200); *Sleep timing variability:* Across-day StD of sleep onset, inter-and intra-day stability; sleep offset, and sleep mid-point; relative activity- adjusted amplitude (Roberts et al., 2020); *Physical activity:* Overall activity, time spent walking, in moderate and physical activity. Timing of maximal physical activity will be used in analyses of rest-activity rhythm. Data will be processed in a customized data management environment that interfaces with Fitbit cloud servers. This platform provides secure data acquisition and management tools that facilitate remote data collection without the need to return devices for data extraction. Using an in-house algorithm that captures continuous heart rate sensor data at 1-5-sec intervals, we will calculate minutes of non-wear time (i.e., absence of a pulse for ≥60 secs), enabling us to determine compliance and distinguish between real and spurious sedentary time. Missing data will be handled using interpolation. Labeled sleep stage data will be retrieved at a granularity of 30s, activity counts at 60s, and the heart rate at 1s. Sleep-wake metrics will be generated using signals from accelerometry, heart rate, and heart rate variability processed by Fitbit’s proprietary, validated algorithm (Dillon et al., 2005). Valid sleep data will be defined as non-nap sleep durations >3 hr. Physical activity will be derived from daily step counts detected by Fitbit’s triaxial accelerometer, which agrees with direct observation, and will be reported as daily and intraday (per minute) step counts. Using step counts, we will calculate minutes spent doing sedentary, light, moderate, and vigorous activity. Metrics will be calculated for each 24-hour period, generating averages and within subject standard deviations (to assess within-subject variability).

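### The Fitbit is issued to measure sleep, but its compliance bonus has no night-wear condition and can be earned with no night recorded

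*Protocol*

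**What the plan says.** Purpose. Under Platforms for Data Collection, the Fitbit Protocol says: "The purpose of the Fitbit portion of the study is to assess whether cannabis abstinence impacts objective measures of sleep". The same paragraph gives the wear instruction: "Participants will then be instructed to wear the device at all times (except when charging the device". It does not say when to charge.

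Bonus. The Actigraphy paragraph under Assessment Techniques sets the condition, in dollars: "25 compliance bonus at each of the three EMA phases data is available for 16/24 hours of 80% of days within that phase". The Remuneration section words it, again in dollars, as "25 for a Fitbit compliance rate of 66% across each of the three phases", and its Table 2 also shows only 66%. Neither of these two places mentions a share of days.

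Measurement and analysis. The exploratory-analyses paragraph under Data analysis derives wear from the pulse signal: "we will calculate minutes of non-wear time (i.e., absence of a pulse for ≥60 secs), enabling us to determine compliance". It adds an analysis rule, "Valid sleep data will be defined as non-nap sleep durations >3 hr", and one sentence on gaps, "Missing data will be handled using interpolation". The sleep outcomes listed there include within-person means and standard deviations (SDs). The list also covers daytime activity and rest-activity rhythm.

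**The concern.** The rule that defines and rewards adherence counts any 16 hours of the day, and the 8 hours that it leaves free are about the length of a night. Charging overnight is an ordinary habit, and the wear instruction exempts charging at any hour. A participant can therefore follow the instruction and collect the full payment while supplying none of the data that the device was issued to collect. A night that was not recorded cannot be recovered later.

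Two further points follow. The bonus is worded differently in two sections, so staff could reach different payment decisions from the same data. In addition, the interpolation sentence does not say how long a gap may be filled. This matters because several sleep outcomes are SDs, which interpolation pulls downward.

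**Working it through.** **Inputs from the protocol.** 16 of 24 hours and 80% of days (Actigraphy paragraph); 66% (Remuneration and Table 2); phases of 14, 7 and 7 days (General Description of Study Design); valid sleep of more than 3 hours, naps excluded (Data analysis).

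**Input assumed.** Nightly sleep length S is not given. A range of 5 to 12 hours is used.

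**1. The plan's own figure.** 16/24 = 66.7%, which agrees with the 66% in Remuneration. The 66% is thus plausibly the same per-day threshold.

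**2. Sleep that the rule forces into wear time.** Hours that may be unworn on a compliant day: 24 − 16 = 8. The least sleep that must be recorded is max(0, 16 − (24 − S)), which equals max(0, S − 8).

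| Sleep S (h) | Waking hours | Least sleep recorded (h) | More than 3 h forced? |
|---|---|---|---|
| 5 to 8 | 19 to 16 | 0 | no |
| 9 | 15 | 1 | no |
| 10 | 14 | 2 | no |
| 11 | 13 | 3 | no |
| 12 | 12 | 4 | yes |

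Only above 11 hours of sleep does the rule guarantee a valid sleep record.

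**3. The two wordings compared.**
- 80% of whole days: 0.80 × 14 = 11.2, so 12 days; 0.80 × 7 = 5.6, so 6 days. Minimum wear is 12 × 16 = 192 of 336 hours, or 6 × 16 = 96 of 168 hours. Both are 57% of phase hours.
- 66% read as a share of all phase hours: 0.66 × 336 = 221.8 h, or 0.66 × 168 = 110.9 h. Wearing the watch for 16 daytime hours every day gives 224 h or 112 h, which still passes with no night.
- On that reading the wordings can disagree. Sixteen hours on 12 of 14 days (192 h) passes the first and fails the second. Twenty-four hours on 10 of 14 days (240 h, 71% of days) fails the first and passes the second.

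**4. Interpolation, for illustration only.** Nights were simulated as independent normal values, a fixed number was removed at random, and the gaps were filled linearly (20,000 series per case). The table gives the mean SD relative to complete data.

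| Nights missing | Interpolated | Recorded nights only |
|---|---|---|
| 1 of 7 | 94% | 99% |
| 2 of 7 | about 87% | 98% |
| 3 of 7 | 80% | 97% |
| 2 of 14 | 95% | almost 100% |
| 4 of 14 | 91% | 99% |
| 6 of 14 | 85% | 98% |

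The protocol gives no rate of missed nights, so these figures show direction and rough size and do not predict what will happen.

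**The case against.** Much can be said for the plan. Participants are told to wear the device continuously apart from charging, and staff sync it at each visit. The 16-hour rule decides a $25 payment, and nothing makes it an inclusion rule for analysis. Every Fitbit analysis is exploratory, Aims 1 and 2 rest on EMA, and the PSQI gives a separate self-reported sleep measure at most visits. Recording no night at all also requires sleep of about 8 hours or less with near-continuous wear while awake; at exactly 8 hours there is no slack. Daytime naps could still be recorded. All of this stands and limits the severity. It does not close the gap, because overnight charging satisfies both the instruction and the bonus.

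Four stronger readings are tempting, and the document does not support them.

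- A reader might infer that unworn nights will be filled by interpolation. The sentence sits between the description of non-wear minutes and the list of sampling intervals in seconds, so it may mean short gaps in the signal. The valid-sleep rule would leave an unworn night without a record, and the Missing Data paragraph names other methods. The text is open on the point.
- A reader might infer that the trial cannot tell whether sleep was measured. It can: pulse data and the valid-sleep rule show which nights are absent. The weakness is in what is rewarded.
- A reader might multiply 16/24 by 80%, get 53%, and say that this contradicts 66%. The two are in different units, and whole days make the minimum 57%. The real discrepancy is that Remuneration omits the share of days.
- A reader might expect night wear to differ by arm or phase and so to bias the comparison. Nothing in the protocol shows this, and the same rule applies to both arms.

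**Conclusion.** The point holds as a minor design weakness. The bonus rule guarantees no recorded night for anyone who sleeps 8 hours or less, and no valid sleep record for anyone who sleeps 11 hours or less. This is true whether the threshold is read per day or as a share of phase hours. The result is arithmetic on the protocol's own numbers. The only assumption is sleep length, and the conclusion covers any plausible value. Zero nights is what the rule permits; it is not a forecast of how participants will behave.

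The mismatch between the two statements of the rule is a separate wording fault and should be reconciled. The possible loss in the SDs, to about 80 to 95% of their true value, depends on whole nights being interpolated and on assumed numbers of missing nights. It is a reason to clarify the sentence and is not an established bias. The EMA analyses are unaffected.

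**What to change.** 1. Keep the 16-of-24-hour condition, because the activity and rest-activity metrics need daytime wear and a sleep-only rule would stop paying for it. Add that a compliant day must also contain a main sleep period that is valid under the existing rule of more than 3 hours, naps excluded. At 80% of days this requires 12 of 14 nights in phase 1 and 6 of 7 nights in each of phases 2 and 3, where the present rule guarantees none.
2. State this one rule identically in the Actigraphy paragraph, the Remuneration text and Table 2, including the share of days.
3. Add one line to the device instructions asking participants to charge during waking hours.
4. In the exploratory-analyses paragraph, limit interpolation to short signal gaps and compute sleep means and SDs on recorded valid nights.

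The cost is small. The wear and sleep data are already collected, so the change is to wording and to the payment check. Slightly fewer participants may earn the $25 in a phase.

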**Platforms for Data Collection**

**Questionnaires Collected via Research Electronic Data Capture (REDCap):** Surveys will be administered via REDCap, a HIPAA compliant, web-based application hosted by Partners HealthCare designed to support data capture for research studies (http://rc.partners.org/edcredcap), at in-person visits (or virtually via MGB-approved video conference platforms like Microsoft Teams or zoom; V1-12).

Data will be stored automatically and securely on a SQL Server, accessed over industry standard TLS 256 bit RSA encryption during data transfers. Data is routinely backed up locally onto a redundancy server and stored in a separate database. Long term storage on Partners servers occurs nightly and allows for incremental backup over multiple systems. Therefore, should one drive be physically damaged, there will be multiples within the chain to replace it. Both data servers are stored within PHS IS corporate firewall, in a secure, key access facility with password-protected computers. Only vetted PHS security officials will have access to physical machines storing study data. Since data are stored on a protected server, a compromise of any individual computer at a research facility will not lead to a breach of the secure database. Individual computers designated for data capture do not store participants’ identifying information or study data.

**MetricWire (iOS & Android OS):** (<https://metricwire.com/>): EMA data capture will occur through Metricwire**,** a secure smartphone-based application with full-cycle project capabilities, including and most importantly for the current project is in-the-moment observation and reporting. This application is easily customizable to build sophisticated protocols using a simple drag-and-drop interface to engage participants under virtually any scenario and capture contextually relevant data. The application can be programmed with more the 60 different types of question formats, has both mobile and web participant-facing applications, and has functionality to notify participants of surveys to-be-completed via push notifications, SMS, voice, and email. Compliance management workflows deliver actionable information to ensure participant safety, maximize response rates and keep the study team on the same page. Relevant to this high-risk cohort, individualized safety plans can be pre-programmed into the application and can be delivered electronically to participants if safety concerns are reported during any EMA prompt type. Metricwire is currently the only EMA platform available that complies with HIPAA, FDA 21 part 11 and GDPR. All data collected will be stored with a unique random ID, making identification from survey responses impossible.

Aim 1: Primary outcomes will be depression items (e.g., bored, sad, tired, irritable) and SI intensity items (presence, urge, controllability) which are measured on a scale of “1 – Not at all” to “100 – Very Much” after each EMA prompt during the phase 1 of EMA.

Aim 2: Primary outcomes will be depression items (e.g., bored, sad, tired, irritable) and SI intensity items (presence, urge, controllability) which are measured on a scale of “1 – Not at all” to “100 – Very Much” after each EMA prompt during phases 1, 2 and 3 of EMA.

**Fitbit Protocol:** The purpose of the Fitbit portion of the study is to assess whether cannabis abstinence impacts objective measures of sleep in school-aged adolescents and young adults. At Baseline, participants will receive a Fitbit 3 that is paired with a premade, de-identified account. At the first visit, participants will be instructed on how to use the device, including charging and syncing. Participants will then be instructed to wear the device at all times (except when charging the device), from Baseline (Visit 1) through Visit 12 (approximately 70 days after Baseline). Participants will be instructed to sync their device frequently throughout the study. At each visit, a member of study staff will also sync the Fitbit to the Fitbit app to pair the deidentified sleep and activity data to the pre-made de-identified account.

**Remuneration**

Participants may be paid between study visits for their participation. The level of compensation is deemed appropriate given the time commitment. Reloadable cards will be managed by Advarra Participant Payments. Advarra Participant Payments is an MGH-approved, secure, web-based platform that facilitates clinical trial and study-related payments onto prepaid reloadable Visa cards. Participants will be informed of Advarra policy during the consent process. After agreeing to participate in the study, participants will also be asked to sign a “Advarra Participant Payment Card Acknowledgement of Receipt” form to certify their understanding of Advarra Participant Payment policies. The form will require participants to print and sign their name and provide their social security number. If the participant is under 18 years old, then parent/guardian information including date of birth, social security number, and address will be collected. Advarra acknowledgment forms will be stored in a locked study cabinet. Given that the scientific objective of this study necessitates implementation of a robust contingency management protocol which requires immediate payment following verification of cannabis abstinence, the primary payment delivery method will be Advarra. If a participant is under the age of 18 and does not have a parent that is willing to provide a social security number, they may be paid via MGB-issued check. Social security numbers will be stored and protected on the MGB-approved, secure REDCap server. Participants will be compensated for attendance of in-person visits, abstinence (if randomized to CB-Abst), plus a compliance bonus at the end of each EMA phase if ≥80% of random prompts are completed. Cannabis abstinence will be indexed by self-reported non-use and, given cannabis’ long half-life, by progressively decreasing quantitative levels of 11-nor-delta-9-THC-9-carboxylic acid (THCCOOH), the primary cannabis metabolite, in urine. Laboratory processing of cannabis metabolites will be conducted at Dominion Diagnostics.

Payments will be made using an escalating scale for abstinence reimbursements and on a consistent scale for EMA compliance (see Tables 1 & 2). The reimbursement schedule was informed by PI’s ongoing contingency management studies and has been effective in other populations (Worden et al., 2017). Maximum total earnings will be matched across group to not confound the potential effects of monetary payments and depressive symptoms and SI. Attendance payments paid via Advarra will be issued at the end of every in-person visit (when participants provide urine samples), abstinence payments will be made between visits when abstinence is biochemically confirmed, and EMA payments will be issued at the end of each of the three EMA phases.

| **Table 2: Max Overall Study Remuneration Schedule** | |
| --- | --- |
| **EMA Compliance Phase 1 (approximately 80%) completion** | $100 |
| **Or: EMA Compliance Phase 1 (approximately 50%) completion** | $25 |
| **Fitbit Compliance Phase 1 (66%) completion** | $25 |
| **EMA Compliance Phase 2 (approximately 80%) completion** | $100 |
| **Or: EMA Compliance Phase 2 (approximately 50%) completion** | $25 |
| **Fitbit Compliance Phase 2 (66%) completion** | $25 |
| **EMA Compliance Phase 3 (approximately 80%) completion** | $100 |
| **Or: EMA Compliance Phase 3 (approximately 50%) completion** | $25 |
| **Fitbit Compliance Phase 3 (66%) completion** | $25 |
| **Study Visits/ Abstinence** | $445 |
| **Overall Fitbit and EMA Bonus (completion across whole study)** | $50 |
| **Max Total Earnings $870** | |

Participants will earn either $100 for a compliance rate of approximately 80% or $25 for a compliance rate of approximately 50% across each of the three EMA phases and $25 for a Fitbit compliance rate of 66% across each of the three phases. Participants can earn an additional $50 if they achieve an overall compliance rate for both Fitbits and EMA phases across the entire study. Payments will be made at the study completion. If a Fitbit device is lost or not returned, 20% of the total earned for this portion of the study will be deducted.

